### Recruitment and eligibility criteria

Eligible participants are adults (ages 18–67) diagnosed according to the International Classification of Diseases version 10 (ICD-10) with schizophrenia, schizotypal, or delusional disorders (F20–F29); or bipolar disorder (F31); or severe depression (F33). Participants must reside in one of two major Danish cities: Copenhagen (including the municipality of Frederiksberg) or Odense. They must be assigned to early intervention teams (OPUS teams) or community mental health services at Mental Health Center Copenhagen or the Department of Mental Health Odense-University Clinic. They must express a clear desire for competitive employment or education and provide verbal and written informed consent. Furthermore, participants must be able to speak and understand Danish well enough to participate without an interpreter, mainly in order to benefit from the group-based cognitive remediation therapy. A connection to vocational authorities with a formalized collaboration with the IPS teams is the foundation for the residence criterion. If this criterion leads to an insufficient number of patients, expansion of the geographic area of the trial will be considered. Participants who are interested in competitive employment or education are identified by case managers, who assess for eligibility and refer to the trial. To ensure that the participants meet the diagnostic criteria, they will be assessed by a trained and certified research assistant using the Schedules for Clinical Assessment in Neuropsychiatry (SCAN) diagnostic tool [22]. Informed consent will be obtained from each participant before assessment.

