### Randomization

After the assessment, a central web-based randomization will be performed by the Copenhagen Trial Unit [23] according to a computer-generated allocation sequence with permuted blocks of varying sizes. The allocation sequence and varying block sizes will be concealed from the investigators. A research secretary will perform the allocation by logging on to a website by using a personal password. Previous research has shown an effect of sex and of work history on vocational outcomes [24, 25]. Therefore, the allocation sequence will be stratified by sex and by work history (more or less than 2 months of competitive employment during the last 5 years). Furthermore, participants will be stratified by work readiness by using match categories, a tool used in Danish job centers [26]. We will assess the likelihood that the participant is ready to apply for competitive employment and will be self-sufficient within 3 months (match 2 or 3). Finally, the participants will be stratified by site.

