Employment specialists in Copenhagen are employed by the vocational authorities in the municipality (job centres) but will still be integrated within the mental health services.

It is expected that many of the participants in the trial will have an aim or motivation to start or resume education. This is expected, firstly, because many of the participants will be young adults recruited from early intervention teams (OPUS) and, secondly, because the education system in Denmark is financed by the state or the municipalities without tuition fees and with the opportunity to receive financial support from the State Educational Grant and Loan Scheme (SU). These options give employment specialists greater opportunities to focus on education compared with previous IPS reports. Employment specialists are encouraged to closely follow the methods described in the updated and expanded IPS manual “Applying the individual placement and support (IPS) model to help clients compete in the workforce” [27]. The manual, including worksheets, is translated into Danish, and the two IPS teams will be trained in the method by an IPS expert, who will also offer tele-supervision throughout the trial period. The IPS employment specialists will be evaluated by trained external reviewers who will use the IPS fidelity scale to ensure high fidelity and adherence to evidence-based practice [28]. The evaluation will take place 6 months after trial start and thereafter every sixth month until high fidelity is demonstrated. Subsequently, an annual evaluation will be performed.

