### Outcome and assessments

The primary outcome is “hours in competitive employment or education” measured from baseline to 18-month follow-up. Employment and enrollment in education will be identified by using register data. Hours in competitive employment will be extracted from an extended version of the Danish Register for Evaluation of Marginalization (DREAM) database administered by the National Labor Market Authority [30]. The DREAM database contains information on employment, sickness leave, and education eligible for state education grants, disability pension, social security, and sickness benefits. The register covers the entire population, and data can be linked to a range of different registers, including the Danish income register, making it possible to obtain the exact number of employment hours. Data on education will be extracted from education statistics hosted by Statistics Denmark (http://www.statbank.dk) and supplemented by data from interviews for more detailed information on part-time studies.

The primary outcome will be supported by several other secondary and explorative outcome measures. Secondary outcomes are work or education at some point during the follow-up period (yes/no), days to first employment or beginning of education, cognitive impairment, functional level, self-esteem, and self-efficacy assessed at baseline and 18-month follow-up. Data on employment and education will similarly be extracted from registers. Furthermore, semi-structured interviews using the Personal and Social Performance (PSP) scale [31] and the Brief Assessment of Cognition in Schizophrenia [32] will be used to assess cognitive impairment and functioning. Standardized validated survey instruments, including the Rosenberg self-esteem scale [33] and the General Self-Efficacy scale [34], will be used to assess self-esteem and self-efficacy. All secondary outcomes and the assessment instruments used are outlined in Table 2.

**Table 2 Tab2:** Primary and secondary outcomes and data collection

Outcomes	Source of collection	Assessment	Baseline	18-month follow-up
Primary outcome	Register-based/Interview	Hours in competitive employment or education in follow-up period		X
Secondary outcomes	Register-based	Competitive employment or education at some point during follow-up period		X
	Register-based	Days to first employment or beginning of education		X

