### Data analysis plan

The main null hypothesis to be tested is that there is no difference between the three groups in hours in competitive employment or education in the 18-month follow-up period. All randomized participants will be analyzed, including those who stop receiving treatment, according to the intention-to-treat principle. All continuous outcome measures, including the primary outcome “hours in competitive employment or education”, will be analyzed by using generalized linear models. In situations in which the continuous measure is non-normally distributed, a non-parametric model will be used. Multiple imputations will be used to impute a distribution of missing values. Furthermore, linear mixed models with repeated measurements and unstructured covariance matrixes will be used to assess the potential interaction between time and intervention. The dichotomous secondary outcome “work or education at some point during the follow-up period” will be analyzed by using logistic regression. The secondary outcome “time-to-employment or education” will be analyzed by using the Cox proportional hazards model. All models will be adjusted for the stratification variables.

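### No stated covariate records prior or current study, although study hours count in the primary outcome; adding one would bring a small precision gain of uncertain size

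*Protocol article*

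**What the plan says.** All places are in the protocol article.

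- **Randomization** names four stratification factors: sex, site, work history and work readiness. Work history is "work history (more or less than 2 months of competitive employment during the last 5 years"). Work readiness is the job-centre match category, read as the likelihood that the participant is "ready to apply for competitive employment and will be self-sufficient within 3 months (match 2 or 3"). Neither definition contains education. The stated reason for two of the factors is "Previous research has shown an effect of sex and of work history on vocational outcomes".
- **Recruitment and eligibility criteria** admits people aiming for either route: "They must express a clear desire for competitive employment or education".
- **Group 1 – IPS** says "It is expected that many of the participants in the trial will have an aim or motivation to start or resume education", and gives as reasons the young adults from early intervention teams and tuition-free education.
- **Outcome and assessments** makes hours in employment or education over 18 months the primary outcome. On the source it says "Data on education will be extracted from education statistics hosted by Statistics Denmark", supplemented by interview. The same section says that the DREAM register holds education eligible for state grants. Table 3 takes register-based social benefits at baseline.
- **Data analysis plan** gives the covariate set: "All models will be adjusted for the stratification variables". It names no other covariate and excludes none.

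**The concern.** The article justifies stratifying on work history because work history predicts vocational outcomes. When the outcome also counts study hours, the same reasoning points to study history, and no such variable is in the stated set.

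The work-history factor may also say little about young participants. For an 18-year-old the 5-year look-back begins at age 13. A student with under 2 months of paid work then falls in the same work-history category as an older person long without work or study, although their expected study hours may differ widely.

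What is at stake is efficiency. In the linear model for hours, any outcome variation that prior enrolment could explain beyond the four existing factors stays in the residual variance and widens the confidence interval.

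**Working it through.** **1. The plan's own figure.** Inputs from Sample size and power calculation: difference 150 h, SD 500 h, type I error 0.0125 (0.05/4), power 80%, 250 per arm. The article does not state sidedness; two-sided is assumed here.

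- Normal approximation: 248 per arm; power at 250 is 0.804.
- t test: 249.4, rounded up to 250; power at 250 is 0.801.

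The stated 250 reproduces.

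**2. Effect of a further covariate.** Let R² be the share of variance in hours explained beyond the stratification factors. The residual SD is 500 × √(1 − R²), and the standard error of a two-arm contrast is that SD × √(2/250). The documents give no value for R², so a range is assumed. Power is for the two-sided t test at 0.0125 with 250 per arm.

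| Assumed R² | Residual SD (h) | SE of contrast (h) | Power | n per arm for 80% |
|---|---|---|---|---|
| 0 | 500.0 | 44.7 | 0.801 | 249.4 |
| 0.01 | 497.5 | 44.5 | 0.806 | 246.9 |
| 0.03 | 492.4 | 44.0 | 0.815 | 241.9 |
| 0.05 | 487.3 | 43.6 | 0.825 | 237.0 |
| 0.08 | 479.6 | 42.9 | 0.839 | 229.5 |

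**3. What R² might be.** For a yes/no covariate with prevalence p and a difference D in mean hours, R² = p(1 − p)D²/SD². All inputs in this step are assumptions.

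- Low: p = 0.2, D = 140 h (20 points × 700 h), SD 600: 0.16 × 19,600 / 360,000 = 0.009.
- High: p = 0.5, D = 300 h (30 points × 1,000 h), SD 500: 0.25 × 90,000 / 250,000 = 0.09.

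These gaps count study hours alone, while the outcome sums study and work. Suppose 25% of the non-study group work 800 h (mean 200 h) and 10% of the study group do (mean 80 h). The high gap then falls to 300 − 120 = 180 h, and R² to 0.25 × 32,400 / 250,000 = 0.032. These values are also marginal: whatever work history, readiness, sex and site already explain has to be taken off.

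**4. Does it need a stratum?** In a simulation with 250 per arm, 20% students and a 400 h gap, the SE of the treatment difference was 44.4 h with neither stratification nor adjustment. With stratification, adjustment or both it was 41.8 to 42.9 h. The theoretical value is √(250,000 − 0.16 × 160,000) × √(2/250) = 42.4 h, so the three agree within simulation error. Adjustment alone delivers the gain. A fifth binary stratifier would double 16 strata to 32, about 23 participants each at 750, and 480 had already been randomized by January 2015.

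**5. Chance imbalance.** With an assumed 35% of students, the SE of the difference in share between two arms is √(2 × 0.35 × 0.65 / 250) = 4.3 percentage points. At a 300 h gap this is about 13 h, or 0.3 of the 44.7 h standard error.

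**The case against.** The strongest reply is that nothing here is wrong. Adjusting for the stratification factors is standard. The Data analysis plan does not rule out further covariates, and a statistical analysis plan that is not shown may add them. The sample size takes no credit for any covariate, so the claimed power does not depend on this one. All of that stands, and it makes the point an improvement to a stated method and not a correction.

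Several stronger readings are tempting and are not supported:

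- *That the treatment comparison is biased or left uncorrected for imbalance.* Randomization remains valid, and the chance imbalance in step 5 is already inside the standard error.
- *That students in general are grouped with the long-term unemployed.* This can apply only to students with under 2 months of employment in 5 years, and no share is given.
- *That nothing in the adjustment predicts who will study.* Sex, site, work history and readiness may each do so in part.
- *That a baseline goal of job or study is available.* Eligibility requires a desire for either; the article does not say that the choice is recorded.
- *That the residual-variance argument extends to all vocational outcomes.* The yes/no and time-to-start outcomes use logistic and Cox models. There, added covariates change the conditional effect being estimated; they do not shrink a residual variance.

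Two further objections limit the gain. The article speaks of starting or resuming education, which suggests that many are not enrolled at entry. The plan also switches to a non-parametric model if hours are non-normal, and the linear gain may not carry over to that.

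**Conclusion.** The mismatch is documented: the outcome covers employment or education, the two work-related baseline factors cover employment only, and no stated covariate records study. The consequence is some forgone precision on hours, with no bias, no invalid test and no error in the sample size.

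The size cannot be derived from the documents, because they give neither a share of students nor the prognostic strength of prior study. Over an assumed incremental R² of 0.01 to 0.08, power at 250 per arm moves from about 0.80 to about 0.805 to 0.84. The lower end is more likely, because people who study may work fewer hours and the existing factors may carry part of the information. This is a worthwhile, near-costless refinement of modest value.

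**What to change.** Keep the randomization strata as they are. Before unblinding, pre-specify as baseline covariates, in addition to the stratification factors:

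1. Education enrolment at or before randomization, taken from DREAM or from the education statistics already used for the outcome.
2. Age.

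Use them in the model for hours. Use the same set in the logistic and Cox models, and fix it in advance there in particular, because it alters the conditional odds and hazard ratios being estimated. Use the participant's stated goal (employment or education) only if it was recorded at entry.

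Cost: one extra register extract, a line or two in the analysis plan and a few degrees of freedom among 750 participants. No additional participants or visits are needed. The benefit may be lost if the non-parametric fallback is used for hours.

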### The experimental interventions

#### Group 1 – IPS

The first experimental intervention group will receive IPS and service as usual (see Control group below). The details of the IPS intervention are described comprehensively in the IPS literature [1, 27] and are briefly outlined below with emphasis on the specific challenges and opportunities for implementation into a Danish context. The IPS intervention is based on eight key principles: (1) eligibility based on client choice, (2) focus on competitive employment or education, (3) integration of mental health and employment services, (4) attention to client preferences, (5) benefits counseling, (6) rapid job search, (7) systematic job development, and (8) individualized long-term job support [1, 7]. Competitive employment is defined as part-time or full-time jobs that exist in the open labor market and that pay at least a minimum wage and are open to everyone, regardless of their disability status [9]. Competitive education is defined as an education or training program that is related to an employment goal and not designed specifically for people with disabilities [27].

Danish employment legislation provides opportunities for financial support when obtaining competitive employment. This could be subsidized employment that in most cases will be consistent with the definition of competitive employment, as it consists of jobs that pay at least the minimum wage and are open to everyone. For more information, see Table 1.

**Table 1 Tab1:** Danish employment legislation

In Denmark, subsided employment at a private workplace is offered to long-term unemployed individuals with or without a disability. Working conditions are agreed upon between authorities and employers and are formalized in a contract. The employee in a private workplace will receive at least minimum wage. Maximum duration of a subsidized job is 1 year, although many will continue in regular employment without subsidy if agreed upon with the employer. Participants will also receive help finding a fleksjob if this is already granted at intake to the study. Fleksjob is also subsidized employment, but the subsidy is conditional on the employee’s ability to work. The employee will receive at least minimum wage for the actual hours of work. The job exists on the open labor market.
Employment specialists in Copenhagen are employed by the vocational authorities in the municipality (job centres) but will still be integrated within the mental health services.

It is expected that many of the participants in the trial will have an aim or motivation to start or resume education. This is expected, firstly, because many of the participants will be young adults recruited from early intervention teams (OPUS) and, secondly, because the education system in Denmark is financed by the state or the municipalities without tuition fees and with the opportunity to receive financial support from the State Educational Grant and Loan Scheme (SU). These options give employment specialists greater opportunities to focus on education compared with previous IPS reports. Employment specialists are encouraged to closely follow the methods described in the updated and expanded IPS manual “Applying the individual placement and support (IPS) model to help clients compete in the workforce” [27]. The manual, including worksheets, is translated into Danish, and the two IPS teams will be trained in the method by an IPS expert, who will also offer tele-supervision throughout the trial period. The IPS employment specialists will be evaluated by trained external reviewers who will use the IPS fidelity scale to ensure high fidelity and adherence to evidence-based practice [28]. The evaluation will take place 6 months after trial start and thereafter every sixth month until high fidelity is demonstrated. Subsequently, an annual evaluation will be performed.

#### Group 2 – IPS enhanced with cognitive remediation and work-related social skills training

The second experimental intervention group will receive IPS (see Group 1 – IPS) enhanced with cognitive remediation and work-related social skills training and service as usual (see Control group below). The cognitive remediation is, with a few adjustments, based on previous research by McGurk et al. [15] and uses an adapted version of the “Thinking skills for work” manual [13, 15]. This is designed as an adjunct to IPS and is aimed at integrating cognitive rehabilitation with the ongoing provision of IPS services. The enhancement program consists of 24 group-based sessions of computer training using newly developed software (CIRCuiTS) and incorporates evidence-based training principles such as errorless learning and massed practice [29]. The computer training provide practices across a broad range of cognitive functions hypothesized to be impaired in persons with severe mental illness, including attention, concentration, psychomotor speed, learning, memory, and executive functions. Each participant works through a so-called metacognitive journey consisting of 278 task instances divided into seven different stages. The participant receives ongoing feedback and is able to monitor their own scores, strategy use, progression in skills, and development or change in personal goals. In addition to receiving the computer training, participants are offered 12 sessions in coping strategies for dealing with cognitive challenges [13]. These sessions are aimed at helping participants develop effective strategies for improving their cognitive skills or reducing the effects of cognitive challenges in order to achieve vocational goals, maintain work, and increase performance [13]. Finally, the program consists of six work-related social skills training sessions with a focus on disclosure, communications skills, decoding norms for social interaction, and conflict management. A detailed manual based mainly on the “Thinking skills for work” manual was developed in Danish but was adapted to the present trial and extended with work-related social skills training. The manual has not been published but can be obtained by request from the authors. The Danish manual further deviates by providing less opportunity for individual training and by implementing CIRCuiTS instead of Cogpack computer software.

The intervention will be performed primarily in group format, and eight participants will be assigned to each group. Trained psychologists will be responsible for the group sessions, and employment specialists will be co-therapists. The program requires 30 weeks to complete, is complementary to IPS, and should not be considered prevocational training. While participating in groups, participants will seek regular employment or education. To ensure the quality of the intervention, employment specialists are trained by psychologists with experience in using the method. A fidelity scale of the intervention has been developed, and fidelity will be assessed at the same time as the IPS fidelity review.

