### Adherence to the interventional program

The employment specialists and the IPS team leaders will assess the use of IPS services, including content and number of contacts between employment specialist and participants. The cognitive specialists will register adherence to the cognitive remediation and social skill groups, including group session attendance and whether home work is completed. In the control group, all contact between the participants and the social worker or vocational counselor will be assessed. It will also be possible to assess whether the controls are allocated to a vocational rehabilitation program of any kind and the duration and content of the rehabilitation. These data will be obtained from the DREAM register and from records in the job centers.

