### Sample size and power calculation

No previous IPS trials or similar studies have been conducted in Denmark that could contribute to an estimation of the expected average number of hours of work among participants in the IPS intervention. A European IPS multicenter trial found a difference between the IPS group and the control group (vocational services) of 150 h in competitive employment in an 18-month follow-up period, and standard deviation was 500 [19]. A difference of 150 h in competitive employment or education is considered clinically relevant. If the outcome within each intervention group is normally distributed with a standard deviation on 500 and with a true mean difference of 150 between the intervention and the control group, the present trial will need 250 participants in both intervention arms and additionally 250 control participants to be able to reject the null hypothesis that the population means of the experimental and control groups are equal with probability (power) of 80 %. The type I error probability associated with the null hypothesis is 1.25 %. A type I error of 1.25 % was chosen to give the possibility to make four comparisons: (1) IPS versus service as usual, (2) IPS versus IPS enhanced, (3) IPS enhanced versus service as usual, and (4) IPS + IPS enhanced versus service as usual. If we encounter difficulties in recruiting 250 participants to each group, we will exclude comparison (4) as a primary comparison. With three primary comparisons, we use a type I error of 1.67 % in the sample size calculation, accumulating a sample size of 236 patients in each group. Power calculations on calculations of the secondary outcome measures were carried out (Table 5) and indicate that a sample size of 250 patients per group would be adequate to detect relevant significant differences.

**Table 5 Tab5:** Power calculation

Outcome measure	δ expected difference in mean	σ expected standard deviation	α	Power	Reference
Days to first employment or beginning of education	68	45	0.0125	1.000 (*t* test)	Bond et al. [8] (2008),
Cognitive function	0.3	0.7	0.0125	0.989 (*t* test)	McGurk et al. [13] (2005)
The Brief Assessment of Cognition in Schizophrenia [32]					
Function measured with Personal and Social Performance (PSP) scale [31]	7	14	0.0125	0.999 (*t* test)	Kawata et al. [31] (2008). Nasrallah et al. [46] (2008) (No IPS studies use PSP scale. δ is estimated)

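### The enhanced arm is treated in groups of eight, but the sample size assumes independent participants and the stated primary model has no term for therapy group

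*Protocol article*

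**What the plan says.** All passages are in the protocol article.

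- **Delivery in the enhanced arm** (section on Group 2): "The intervention will be performed primarily in group format, and eight participants will be assigned to each group". The programme takes 30 weeks, and participants look for work or education while they attend. On staffing: "Trained psychologists will be responsible for the group sessions, and employment specialists will be co-therapists".
- **IPS in both experimental arms.** The same section states: "The second experimental intervention group will receive IPS". The Group 1 section adds that "the two IPS teams will be trained in the method by an IPS expert". The article gives neither the number of specialists nor their caseload, and does not say whether one specialist serves both arms.
- **Sample size** (Sample size and power calculation): "A difference of 150 h in competitive employment or education is considered clinically relevant", and the calculation begins "If the outcome within each intervention group is normally distributed with a standard deviation on 500 and with a true mean difference of 150". It arrives at 250 per arm for 80 % power at a type I error of 1.25 %, chosen to allow four comparisons. No ICC or design effect appears.
- **Analysis** (Data analysis plan): continuous outcomes, including the primary, "will be analyzed by using generalized linear models", or by a non-parametric model if not normally distributed. Adjustment is for the stratification variables (sex, work history, work readiness, site). The mixed models named there are for repeated measurements over time, not for therapy groups or specialists.

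**The concern.** People who spend 30 weeks in the same small group, with the same psychologist and co-therapist, may have more similar outcomes than people in different groups. The shared exposure acts while they are job-seeking, so it bears directly on hours worked or studied. Any positive correlation makes the variance of the enhanced arm's mean larger than 250 independent people would give.

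Two things are at stake, and they are alternatives. If the analysis ignores the correlation, the standard error is too small and the actual type I error exceeds the 1.25 % on which control over the four comparisons rests. If the analysis allows for it, the error rate is right but power falls short of the stated 80 %.

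A similar argument can apply to employment specialists in the IPS arms, but it rests on more assumptions.

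**Working it through.** **Inputs from the article:** difference 150 h, SD 500 h, alpha 0.0125 per comparison, 250 per arm, groups of m = 8 in the enhanced arm (250/8, about 31 groups). **Assumed:** the ICC, shown as a range, and for specialists the number of participants each has in an arm.

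**1. Reproducing the plan's figure.** Two-sided, z(0.0125) = 2.498 and z(80 %) = 0.842.

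n = 2 × (500/150)² × (2.498 + 0.842)² = 248 per arm, against the stated 250.

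At 250, SE = 500 × √(2/250) = 44.72 and power = Φ(150/44.72 − 2.498) = Φ(0.856) = 80.4 % (80.1 % with the t distribution). The fallback of 236 per group at 1.67 % also agrees closely (233). Both follow with a design effect of exactly 1.

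**2. Groups of eight, enhanced IPS against service as usual.** Only the enhanced arm is inflated:

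- DE = 1 + (8 − 1) × ICC
- SE = 500 × √(DE/250 + 1/250)
- power with corrected SE = Φ(150/SE − 2.498)
- actual type I error with uncorrected SE = 2[1 − Φ(2.498 × 44.72/SE)]

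| ICC (assumed) | DE | SE ratio | Power, corrected SE | Type I error, uncorrected SE | n per arm for 80 % |
|---|---|---|---|---|---|
| 0 | 1.00 | 1.000 | 80.4 % | 1.25 % | 248 |
| 0.01 | 1.07 | 1.017 | 78.8 % | 1.4 % | 257 |
| 0.02 | 1.14 | 1.034 | 77.2 % | 1.6 % | 266 |
| 0.05 | 1.35 | 1.084 | 72.5 % | 2.1 % | 292 |

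Power reaches exactly 80 % when 150/SE = 3.339, so SE = 44.92, DE = 1.018 and ICC = 0.018/7, about 0.0025. That is all the slack there is.

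The power and type I columns do not occur together. With the uncorrected SE at ICC 0.05, power is Φ((150 − 2.498 × 44.72)/48.48) = Φ(0.79), about 78.5 %, not 72.5 %.

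**3. The other comparisons, under group clustering.**

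- *Enhanced IPS against IPS:* same formula and same figures at a 150 h difference, because one arm is grouped and the other is not.
- *IPS against service as usual:* neither arm has these groups, so there is no effect.
- *Both IPS arms pooled against service as usual:* SE = 500 × √(1/250 + 0.25 × DE/250 + 0.25/250). Power is 91.5 % with no clustering, 91.2 % at ICC 0.01 and 89.7 % at ICC 0.05.

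**4. Specialists, IPS against service as usual.** DE = 1 + (m − 1) × ICC in the IPS arm only, ICC 0.02 assumed.

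- m = 10 in the arm: DE = 1.18, power 76.3 % (corrected SE) or type I error 1.7 % (uncorrected SE).
- m = 20 in the arm: DE = 1.38, power 71.8 % or type I error 2.2 %.

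**5. Specialists, enhanced IPS against IPS.** If each specialist serves both arms in balance, the specialist effect is common to both means and cancels. The ratio of true to uncorrected SE is then √(1 − ICC) = √0.98 = 0.990, so the uncorrected SE is very slightly too large.

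All figures use the normal approximation. With few clusters a t reference would lower power a little further.

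**The case against.** **The size depends on quantities the article does not give.** This stands. No ICC is stated for hours worked. At 0.01 the groups cost 80.4 − 78.8 = 1.6 points of power. The specialist figures also need an assumed caseload. Site adjustment would absorb differences between the two IPS teams if there is one per city, though not differences between specialists or groups within a city.

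**A separate analysis plan may add cluster terms.** This stands in part. The article's analysis section is short, and a model described as a generalized linear model does not exclude robust errors. But the section does name the primary model and its adjustment variables. An analysis plan also cannot alter the power statement, which the Discussion presents as a strength of the design.

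**Controls may be clustered too.** Fair. The control section mentions group programmes, case management and job-centre support. Treating controls as unclustered is an assumption.

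**Stronger readings the documents do not support.** A reader might infer that every primary comparison has too small a standard error and falls short of 80 % power. The groups do not touch IPS against service as usual, which is the primary hypothesis, and the pooled comparison keeps about 90 % power under group clustering. A reader might also infer that specialists shared by the two IPS arms inflate the error of enhanced IPS against IPS. Sharing is plausible but not stated, and if it occurs the effect largely cancels there.

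**Conclusion.** The point holds for the two comparisons of the enhanced arm with a single other arm. The article fixes treatment in groups of eight, while its 80 % power follows only from independent observations and its stated primary model has no group term. Any ICC above about 0.0025 takes these comparisons below 80 %. Over assumed ICCs of 0.01 to 0.05, the consequence is either power of 78.8 % to 72.5 % or an actual type I error of 1.4 % to 2.1 %, depending on whether the standard error is corrected.

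For IPS against service as usual the point is conditional: it applies only if specialists differ in success. With 10 to 20 participants per specialist in the arm and an ICC of 0.02, all assumed, power is about 76 % to 72 %.

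The loss is modest at small ICCs. It is worth correcting because there is no slack in the calculation and the 1.25 % level carries the control over multiple comparisons.

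**What to change.** **Data analysis plan.** For the primary comparisons, use either cluster-robust standard errors with a small-sample correction or a partially nested mixed model. The clusters are the remediation group in the enhanced arm and the first-assigned employment specialist in the IPS arms. Define both by initial allocation, whether or not the participant attended, so that intention-to-treat is kept. Treat controls as unclustered and state this as an assumption. The small-sample correction matters because clusters are few: about 31 groups, and at the assumed caseloads 250/20 to 250/10, or roughly 13 to 25, specialists per arm.

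**Sample size and power calculation.** State that 80 % power assumes no clustering, and give the range above with its assumed ICCs and caseloads.

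**Data.** The section on adherence already plans to record use of IPS services, "including content and number of contacts between employment specialist and participants", and attendance at group sessions. Group and specialist identity should be obtainable from these records; confirm that they are kept.

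**Costs.** Intervals become slightly wider and the stated power less favourable. There is also a conflict to manage with the Blinding section, under which results coded X, Y and Z are interpreted before the code is broken. An arm with groups of eight, or without any clusters, is recognisable from its structure. The clustered analysis should therefore be run from a pre-specified program with masked cluster codes, and only the X/Y/Z results passed to those who draw the blinded conclusions.
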